### 2.12. Statistical Methods

Descriptive statistics and frequency distributions will be used to present the demographic and clinical characteristics of the study population. The chi square test (or Fisher exact test) will be used to assess potential differences in the prevalence of dental anomalies (specifically hypodontia) in children with and without MIH. The *p* value for statistical significance will be set at <0.05. In addition, logistic regression will be employed to determine the odds ratio (OR) and 95% confidence interval (CI) for the association between MIH and hypodontia (or any specific dental anomaly), after adjusting for age, gender, ethnicity/country, and MIH severity.

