## 1. Introduction

### 1.1. Background and Rationale

One of the most common disorders affecting tooth formation is molar incisor hypomineralisation (MIH), a variable developmental hypomineralised defect of enamel involving the first permanent molars and often the incisors, with an estimated global prevalence of 13% [1]. The management of children with MIH presents numerous challenges relating to the sensitivity and post-eruptive breakdown of affected molars, poor enamel bonding characteristics, and psychosocial concerns about incisor opacities [2,3]. Despite its common occurrence, speculation still surrounds its aetiology, as it is likely that several systemic and genetic and/or epigenetic factors are involved [4]. Within paediatric dental practice, a wide variety of other anomalies in tooth development are also seen, namely, relating to tooth number, morphology, and eruption. The reported prevalence of each of these different dental anomalies is highly variable, depending on the diagnostic criteria employed, as well as the characteristics of the study population [5,6]. Some dental anomalies, notably tooth number, appear to have a gender predilection; supernumerary teeth are twice more common in males than females, whereas hypodontia is more common in females than males [5]. Studies have also reported potential ethnic variation in the presentation of certain developmental dental conditions, with a systematic review reporting significant worldwide disparity in hypodontia prevalence, ranging from 4.4% in Latin America/Caribbean to 13.4% in Africa [7]. Most studies appear to show no gender difference in MIH but, to date, differences according to ethnicity have not been fully explored [1].

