### 2.7. Sample Size

Based on the prevalence estimates of hypodontia in MIH (0.12 [17]) and non-MIH children (0.064 [7]), a sample size of 1168 children (584 per group) would provide 90% power in detecting the statistically significant difference in the association between MIH and hypodontia. The alpha error was set at 5%. Each of the 15 participating countries would, therefore, aim to recruit approximately 80 children (40 MIH and 40 non-MIH). This sample size was calculated using the G Power software (Version 3.1.9.7).

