## 3. Preliminary Results

To date, 39 paediatric dentists from the participating countries have undertaken training and calibration for the use of the MIH index [19]. Overall, 79.5% (n = 31) achieved substantial agreement (or above) on their first attempt; 15.4% (n = 6) repeated the training and subsequently reached the required level of agreement. However, two participants have yet to repeat the training exercise and thus cannot contribute to data collection until calibrated to the required standard. Excellent intra-examiner agreement was found for scoring both enamel defect type and extent (mean k = 0.86 and k = 0.83 respectively). Inter-examiner agreement was slightly lower, with a mean score of k = 0.74 for defect type and k = 0.74 for its extent.

With respect to measuring the degree of taurodontism, 24 paediatric dentists, from the different participating countries, undertook the training and calibration exercise. Overall, 87.5% (n = 21) achieved substantial agreement (or above) on their first attempt; 12.5% (n = 3) are still to repeat this training before progressing to data collection. Intra-examiner repeatability was almost perfect, with a mean kappa score of 0.95. Inter-examiner repeatability was substantial, with a mean kappa score of 0.65. Lack of agreement between examiners was predominantly related to uncertainty as to whether a tooth could actually be assessed; in cases where the crown cusps were not clearly visible, some examiners felt that they could not accurately identify the necessary landmarks. Further clarification has now been provided to investigators.

At the time of writing (April 2023), recruitment had reached 831 children (395 MIH and 436 non-MIH) from all 15 participating countries.

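### The article pairs an unadjusted hypodontia comparison with a regression and does not say which decides; the first is open to sex and country confounding, and the second adjusts for MIH severity

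*Protocol article*

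**What the plan says.** Section 2.12 (Statistical Methods) of the protocol article states: "The chi square test (or Fisher exact test) will be used to assess potential differences in the prevalence of dental anomalies", with hypodontia singled out. The next sentence sets significance at p below 0.05. A logistic regression then follows as a further analysis. It gives an odds ratio and 95% confidence interval for MIH and hypodontia, adjusted for age, gender, ethnicity/country and MIH severity. The abstract also lists a chi-squared test and a regression. Neither place says which analysis settles the null hypothesis of section 1.3.

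The sample size in section 2.7 rests on two unadjusted prevalences, 0.12 with MIH and 0.064 without: "a sample size of 1168 children (584 per group) would provide 90% power". The same section sets the country target: "Each of the 15 participating countries would, therefore, aim to recruit approximately 80 children (40 MIH and 40 non-MIH". No quota or matching on sex or age is described.

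Section 1.1 reports regional hypodontia prevalence "ranging from 4.4% in Latin America/Caribbean to 13.4% in Africa", says hypodontia is commoner in females, and cites an MIH series with 16.1% in girls and 2.6% in boys. It also says most studies find no sex difference in MIH. Section 2.8.2 records severity and extent for MIH teeth only.

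**The concern.** Both groups are clinic attenders, so nothing in the design balances them on sex or age, and only an approximate quota balances them by country. The article names region and sex as predictors of the outcome. A pooled comparison that ignores such predictors attributes to MIH any difference caused by the mix of countries or sexes. It could produce an association that does not exist or hide one that does.

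The planned regression should guard against this, but as written it includes a covariate that cannot be separated from MIH status. If the two analyses disagree, the article gives no rule for choosing, and neither is fully satisfactory as specified.

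**Working it through.** **1. The plan's own figure.** Inputs from section 2.7: 0.12 against 0.064, alpha 5%, 584 per group. Sidedness is not stated; two-sided is assumed. The exact power of an unstratified Fisher test at 584 per group is 0.9005, so the stated 90% reproduces. The normal-approximation sample size is 558 per group without continuity correction and 593 with it. The sample size is therefore built on the unadjusted comparison. The planned effect is 5.6 points, an odds ratio of (0.12/0.88)/(0.064/0.936) = 1.99.

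**2. Country, quotas met.** Assume 15 country prevalences evenly spaced from 4.4% to 13.4%, 40:40 in each, and no MIH effect within any country. The type I error of the pooled chi-square is 4.9%, so there is no bias.

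**3. Country, quotas missed in a patterned way (assumed).** Take 13.4% in Egypt, Nigeria and Sudan, 4.4% in Chile and 6.4% in the other 11 countries. The split is 30:50 in each African country, 40:40 in Chile, and the remainder is spread over the other 11 so that each group totals 600. There is no true association.
- MIH: (90 × 0.134 + 40 × 0.044 + 470 × 0.064)/600 = 43.90/600 = 7.3%
- Non-MIH: (150 × 0.134 + 40 × 0.044 + 410 × 0.064)/600 = 48.10/600 = 8.0%
- Crude odds ratio: (0.0732/0.9268)/(0.0802/0.9198) = 0.91

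With the evenly spaced prevalences of step 2, and MIH shares rising across countries in step with prevalence, the type I error of the pooled test is:

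| MIH share across countries | Type I error |
|---|---|
| 45–55% | 5.5% |
| 40–60% | 7.0% |
| 35–65% | 9.6% |
| 30–70% | 13.3% |

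**4. Sex (assumed).** Girls are 60% of the MIH group and 50% of the comparison group, with 584 per group and no true association.
- Rates of 16.1% and 2.6% applied to both groups: 0.6 × 16.1 + 0.4 × 2.6 = 10.70% against 0.5 × 16.1 + 0.5 × 2.6 = 9.35%. The spurious difference d is 1.35 points, and the odds ratio is 1.16.
- Pooled standard error: se0 = √(0.10025 × 0.89975 × 2/584) = 0.0176. The unpooled value se1 is the same to three figures.
- Type I error: Φ((d − 1.96 se0)/se1) + Φ((−d − 1.96 se0)/se1) = Φ(−1.19) + Φ(−2.73) = 0.117 + 0.003 = 12.0%.
- Milder case, with an assumed female:male ratio of 1.4 around 6.4%: boys 5.33%, girls 7.47%. The difference is 0.21 points, the odds ratio 1.04 and the type I error 5.3%.

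**5. Check on the remedy.** In 10,000 simulated studies per scenario (country shares equal, 40–60% and 30–70%; girls 50%, 60% and 69.6% of the MIH group), a Mantel-Haenszel test stratified by the factor concerned kept type I error between 4.7% and 5.4%. The pooled test reproduced the approximations above, for example 11.7% at 60% girls.

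**6. The severity covariate.** Children without MIH have no severity value, which leaves three codings:
- If severity is left missing, every comparison child drops out and MIH is constant.
- If it is coded as categories with a no-MIH level, the MIH indicator is the sum of the remaining levels and is not separately estimable.
- If it is coded as a score with zero for non-MIH, the MIH coefficient refers to MIH of zero severity, which is not the overall association sought.

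**The case against.** The strongest reply is that adjustment is already planned: the regression includes age, gender and ethnicity/country, which are the confounders at issue. The chi-square is never called primary, and the sentence on the threshold is not expressly confined to it. A condensed article may also leave the order of analyses to an analysis plan that is not shown. All of that stands. It rules out any claim that confounding has been ignored, or that the chi-square is the declared deciding test. It does not rescue the regression, because the adjustment set is stated here and includes severity.

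The design also works against country confounding. If the 40:40 quotas are met, the pooled test is sound on that axis (step 2). Section 1.1 gives no reason to expect a sex imbalance, since most studies find none in MIH.

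A reader might take the interim count in section 3, "recruitment had reached 831 children (395 MIH and 436 non-MIH", as evidence that bias has already arisen. It is not. An unequal overall ratio biases nothing; only an MIH share that varies across countries together with prevalence would, and no breakdown by country or sex is given. Recruitment was also still open.

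A reader might also infer a strongly female MIH group from the cited series, since (12 − 2.6)/(16.1 − 2.6) implies about 70% girls. Against 50% in the comparison group, that would give a type I error of 31%. But this is one series of 101 children, and nothing shows that its sex mix will recur.

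Nor does the slash in ethnicity/country show that the two will be coded as one variable.

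**Conclusion.** The concern holds in a limited form. The article puts an unadjusted test of a non-randomised comparison beside the significance threshold, adds a regression for the same question, does not say which decides, and gives the regression an adjustment set that cannot deliver the overall MIH association.

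Bias in the unadjusted p-value is conditional and not demonstrated. It needs a sex imbalance, or departures from the country quotas in step with prevalence. With quotas met and sex balanced, the type I error is about 5%. In the assumed scenarios the effect ranges from negligible (about 5% with 60% girls and a 1.4 sex ratio) to about 12% with 60% girls at the 16.1%/2.6% rates. The latter is an upper-end case, because it applies rates from MIH patients to both groups and so puts the comparison group at 9.35% against the planned 6.4%. The spurious odds ratios of 0.91 and 1.16 are small beside the planned 1.99.

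These results assume a two-sided test, the country prevalences shown, and 50% girls in the comparison group. The change is worth making because it removes an avoidable risk at almost no cost, not because the main result is shown to be wrong.

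**What to change.** State in section 2.12 that one analysis decides the primary question: logistic regression of hypodontia on MIH, adjusted for age, sex and country, without MIH severity. A Cochran–Mantel–Haenszel test stratified by country and sex is a simple alternative. Keep the pooled chi-square or Fisher test as descriptive. Examine severity in relation to hypodontia within the MIH group only, where it is defined.

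The cost is a change of wording before analysis. Age, gender, ethnicity/country and severity are already on the record form, and no further recruitment or measurement is needed.

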## 2. Materials and Methods

### 2.1. Overall Study Design

This will be a cross-sectional analytical study involving children with MIH and a comparison group of non-MIH-affected children.

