### 2.5. Outcomes

The primary outcome measure for this study is the presence or absence of MIH and its association with the presence of another dental anomaly (specifically hypodontia) in the participants. Details of the index used to score the enamel defect are described in Section 2.8 below.Secondary outcome measures for this study include the clinical and/or radiographic severity of MIH in relation to participants’ gender, ethnicity/country, and their global self-reported oral health, details of which are also provided in the subsequent Section 2.8.

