#### 2.8.2. Clinical Variables

-The primary dental diagnosis will be recorded for both MIH and comparison participants (e.g., the comparison group could include patients presenting with orthodontic concerns, dental caries, traumatic dental injury, oral pathology/oral medicine-related issues, tooth surface loss, periodontal condition, or no dental condition but medical/behavioural reason for referral).-Any known close family history (siblings or parents) of enamel defects, or missing or extra teeth, will be documented.-Any enamel defect will be recorded using the validated MIH index [19,20]. All permanent teeth and second primary molars will be included, with scores given according to the nature of the defect (MIH or non-MIH) and, for MIH teeth, the severity and extent of the defect will also be recorded.-Any other anomalies detected clinically will be noted, including: microdontia of permanent maxillary lateral incisors, dens invaginatus/evaginatus, double teeth, erupted supernumerary teeth, infraocclusion of primary molars (categorised as >1 mm below occlusal level of adjacent tooth/teeth), and ectopic eruption of first permanent molars.

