A further justification for undertaking this study is the potential to correlate not just the presence of MIH, but the severity of the condition, particularly the status of the first permanent molars (in terms of tooth tissue loss and sensitivity) with other dental anomalies and the presence/absence of developing third permanent molars. This line of inquiry would give valuable clinical insights to aid diagnosis and treatment planning for children with MIH, with the unique opportunity of exploring any ethnic/country differences. Despite a rapidly growing evidence base on the epidemiology, aetiology, and presenting characteristics of MIH, no standardised study has ever been conducted across such diverse populations.

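### The only adjusted model for the MIH–hypodontia odds ratio also adjusts for MIH severity, which comparison children cannot have, so its MIH term is not estimable or does not measure MIH versus no MIH

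*Protocol article*

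**What the plan says.** Section 2.12 (Statistical Methods) sets out two inferential steps. The first is unadjusted: "The chi square test (or Fisher exact test) will be used to assess potential differences in the prevalence of dental anomalies". The second is a logistic regression giving an OR and 95% confidence interval "for the association between MIH and hypodontia (or any specific dental anomaly"; its covariates are introduced by "after adjusting for age, gender, ethnicity/country, and MIH severity". No other adjusted model is stated.

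Two other sections determine who can have a severity value. Section 2.8.2 (Clinical Variables) says that "for MIH teeth, the severity and extent of the defect will also be recorded". Section 2.1 (Overall Study Design) sets the MIH children against "a comparison group of non-MIH-affected children".

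Elsewhere the article treats severity as something to study, not something to adjust away. Section 2.5 (Outcomes) reads "Secondary outcome measures for this study include the clinical and/or radiographic severity of MIH", and the Discussion points to "the potential to correlate not just the presence of MIH, but the severity of the condition".

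**The concern.** Severity is a grading of the exposure. Any child with a graded severity has MIH, and any child without MIH has none. It therefore cannot confound the comparison of MIH with no MIH. Conditioning on it while also estimating an MIH effect asks the model to separate two things that the design does not separate, and a larger sample does not help.

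The regression is the article's only stated control for age, gender and ethnicity/country in an observational, clinic-based comparison. The Introduction (section 1.1) itself reports that hypodontia differs by gender and by world region (4.4% to 13.4%). Section 2.12 applies the same model to any specific anomaly, so the adjusted ORs for the secondary anomalies share the fault.

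**Working it through.** **Inputs from the article.** Section 2.7 gives hypodontia prevalence 0.12 (MIH) and 0.064 (comparison), 584 children per group, 90% power and alpha 5%. Sidedness is not stated; two-sided is assumed.

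**Assumed, because the article does not give them.** A child-level severity score, its number of grades, the split between grades, and the hypodontia prevalence in each grade. Age, gender and country are left out of the calculations; they do not remove the dependence.

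**The plan's own figure.** Exact two-sided Fisher power for 0.12 versus 0.064 is 0.89999 at 583 per group and 0.90054 at 584, so 584 is reproduced. The usual normal formula gives 558 without and 593 with continuity correction.

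**Reference model, without severity.**
- logit(0.12) = −1.992; logit(0.064) = −2.683; difference 0.690, so OR = 1.99.
- SE = √[1/(584×0.12×0.88) + 1/(584×0.064×0.936)] = 0.21; 95% CI 1.32 to 3.02.

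**Coding 1: severity missing in comparison children.** A complete-case fit drops all 584 of them. MIH is then constant, the design [1, MIH, severity] has rank 2 of 3, and there is no MIH OR.

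**Coding 2: severity as categories, with 'none' as a level.** The MIH column is the exact sum of the severity indicators. With mild and severe, [1, MIH, mild, severe] has rank 3 of 4. If software drops one grade, the MIH term becomes that grade versus comparison. With three grades at 6/12/18%, it is 0.93 if mild is dropped and 3.21 if severe is dropped.

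**Coding 3: numeric score, comparison children = 0.** The model fits. With mild = 1 and severe = 2, the MIH coefficient extrapolates the line through the two grades back to severity 0:

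log OR = 2·logit(p_mild) − logit(p_severe) − logit(0.064)

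With an equal split (292 per grade), its variance is 4/[292·p_mild(1−p_mild)] + 1/[292·p_severe(1−p_severe)] + 1/[584·0.064·0.936].

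| Mild / severe | log OR | OR | SE | 95% CI |
|---|---|---|---|---|
| 12% / 12% | 0.690 | 1.99 | 0.44 | 0.85 to 4.69 |
| 11% / 13% | 0.402 | 1.50 | 0.45 | 0.62 to 3.58 |
| 10% / 14% | 0.104 | 1.11 | 0.46 | 0.45 to 2.72 |
| 8% / 16% | −0.544 | 0.58 | 0.49 | 0.22 to 1.52 |

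Mean MIH prevalence is 12% in every row. Setting the log OR to zero gives p_mild of about 9.7% (severe about 14.3%); the OR is below 1 only if mild prevalence is lower than that. In the first row, approximate power for the adjusted OR is Φ(0.690/0.437 − 1.96) = 35%, against Φ(0.690/0.212 − 1.96) = 90% without severity. The SE in that row depends on the split: 0.52 with 30% mild and 0.42 with 70% mild.

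**Three-grade score (1, 2, 3; equal thirds), comparison children = 0.** Fits to expected counts give:
- 12/12/12%: OR 1.99 (0.95 to 4.18)
- 8/12/16%: OR 0.89 (0.40 to 1.99)
- 6/12/18%: OR 0.56 (0.24 to 1.31)
- 18/12/6%: OR 5.99 (2.99 to 12.03)

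The bias can therefore run in either direction.

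**Coding 4: score centred within the MIH group, comparison children = 0.** The OR stays between 1.69 and 1.99 over no gradient and rising gradients up to 4/12/20%. The article does not state this coding.

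**The case against.** The main comparison is not touched. The primary objective in section 1.2 is a prevalence comparison, section 2.12 tests it by chi-square or Fisher without severity, and the sample size fits that test. The regression is introduced as an addition. This stands. A reader might infer that the study's 90% power falls to about 35%; it does not, because that figure belongs to the adjusted OR under one assumed coding with no gradient.

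A reader might also infer that a true dose-response would turn the MIH OR protective. The arithmetic does not support that: 11%/13% and 10%/14% are real gradients and give ORs of 1.50 and 1.11. Even at 8%/16% the interval around 0.58 includes 1. Reversal is possible but not inevitable, and a falling gradient does the opposite.

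In practice, aliasing under categorical coding would probably show at the first fit and force a respecification, and centring within MIH would largely preserve the OR. The covariate list may simply be loose wording; the Abstract describes the regression as relating anomalies to patient characteristics. These points reduce the likely practical harm. They do not rescue the text. An unseen analysis plan could supply coding detail, but the article itself fixes the adjustment set, and that set is wrong for the OR it names. An analyst who follows it gets no usable MIH OR unless an unstated coding is chosen; one who departs from it deviates from the published plan.

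**Conclusion.** The point holds as an error in a stated rule, not as missing detail. With severity in the model, the MIH OR is either not estimable (severity missing or categorical) or, with a numeric score and comparison children at 0, not an estimate of MIH versus no MIH.

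That the MIH term is unusable or redefined under these codings follows from the article alone. The sizes do not: they rest on assumed scores, splits and gradients. Within those assumptions, against a severity-free OR of 1.99, the reported value ranges from 0.56 to 5.99, and with no gradient the standard error of the 1/2 score roughly doubles.

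The damage is confined to the adjusted ORs, for hypodontia and for the secondary anomalies. Those are the only confounder-adjusted estimates the article offers, so the wording should be corrected before analysis.

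**What to change.** In section 2.12, remove MIH severity from the covariates of the MIH-versus-non-MIH model, leaving age, gender and ethnicity/country. Add a separate severity analysis in one of two forms: a model in which a graded exposure (none, mild, up to severe) replaces the MIH indicator, with a trend test if wanted; or a model within the MIH group only. Apply the same change to the models for the other anomalies. State how tooth-level severity becomes a child-level grade.

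The cost is a few lines of analysis wording, declared as a change to the published plan. Recruitment, data collection, the sample size and the chi-square or Fisher comparison stay as they are.
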